### Sample size

The sample size estimate was based on the RCT of the same dose and preparation of EPA-FFA in FAP patients [15], a meta-analysis of aspirin RCTs [22] and detailed 2007–2008 BCSP audit data from the South of Tyne and Tees BCSP Centres.

In order to detect a minimum 18% relative reduction in adenoma risk in each two-arm comparison (less than the 22% reduction in polyp number compared with placebo in the FAP Trial [15] and below the absolute reduction in polyp number at one year [38%] in the aspirin RCTs [22]) from a 60% adenoma recurrence rate (South of Tyne and Tees BCSP data) at surveillance colonoscopy to 49%, 678 evaluable ‘high risk’ individuals need to be randomized equally to the four treatment arms, with 80% power at a 5% two-sided significance level. Standard practice for 2 × 2 factorial designs in the assumed absence of any interaction bases the sample size estimate on comparison ‘at the margins’ of active treatment A vs. placebo A (half of whom in each arm receive active treatment B and the other half placebo B). Assuming the same target effect size and alpha, this yields the same power for the marginal comparison of active treatment B vs. placebo B (half of whom in each arm receive active treatment A and the other half placebo A). With a total sample size of 678 for analysis, there is, in fact, a slight reduction in power (to 75%) which arises if *both* treatments work, because then the overall comparison for treatment A is not 0.49 vs. 0.6, but is 0.445 vs. 0.545 (averaging over the placebo and treatment B arms). To keep power at 80% for the above figures, 192 individuals are required per arm (total 768 evaluable ‘high risk’ individuals). Allowing for a 15% drop-out rate increases the sample size to 768/0.85 = 904 individuals.

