#### Descriptive analyses

The baseline comparability of the groups will be assessed with regard to the following variables: age at randomization, gender, body mass index, cigarette smoking, alcohol consumption, diagnosis of diabetes, requirement for a repeat colorectal endoscopic procedure within 3 months, number of adenomas detected at baseline, number of ‘advanced’ adenomas detected at baseline and the location of adenomas in the colorectum. Categorical (including binary) variables will be summarized by reporting numbers and percentages in each category, continuous variables will be summarized using means and standard deviations. Missing data will be tabulated.

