#### Primary analyses

For the primary outcome, it is anticipated that the 2 × 2 factorial trial will be analysed by an ‘at the margins’ approach, after first examining whether there is any evidence of an interaction between EPA and aspirin [29], although it is recognized that this will lack power to detect anything but a very large interaction effect. The log relative risk will be estimated using a log-binomial regression model with robust standard errors to allow for potential non-independence of observations within a BCSP centre. Both interventions will be fitted simultaneously and in a further secondary analysis, adjusted for ‘repeat colorectal endoscopic procedure within 3 months required’ plus any other covariates identified as important from the baseline comparisons. Should there be strong evidence of an interaction between EPA and aspirin, the effect of each treatment alone will be examined using an ‘inside the table’ approach, although it is recognized that precision for these analyses may be reduced since each uses only approximately 50% of the available sample.

A per-protocol analysis will be conducted as a sensitivity analysis, where the per-protocol population consists of all randomized participants who were not deemed to have a protocol violation. Additionally, some BCSP centres consist of multiple hospitals (sites), therefore an additional sensitivity analysis will be conducted in which both BCSP centre and site will be treated as random effects in a multi-level model.

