#### Secondary analyses

All secondary end-points will be analysed using the ITT population, with the exception of adverse events, for which we will analyse the safety population, consisting of all participants who received at least one dose of trial medication.

• The relative recurrence of ‘advanced’ adenoma detected at the first BCSP surveillance colonoscopy will be analysed using a log-binomial regression model with robust standard errors to estimate the log relative risk.

• Number of ‘advanced’ adenomas per participant at the first BCSP surveillance colonoscopy will be analysed using a Poisson regression model with robust standard errors.

• Number of adenomas per participant at the first BCSP surveillance colonoscopy will be analysed using a Poisson regression model.

• The region of the colorectum where adenomas are detected at the first BCSP surveillance colonoscopy will be explored, possibly using a Poisson random effects model with bivariate response (corresponding to polyp counts in the left and right colon) in which treatment and a baseline polyp count will be independent variables together with random intercepts corresponding to patient and BCSP Centre.

• The number of ‘high risk’ participants re-classified as ‘intermediate risk’ after the first BCSP surveillance colonoscopy will be analysed using binary regression or logistic regression, treating centre as a random effect.

• The number of participants with CRC detected prior to or at the first BCSP surveillance will be analysed descriptively, and possibly using a logistic regression model depending on numbers with this outcome, although it is anticipated that there will be low power due to small numbers.

Adverse events, including clinically significant bleeding episodes will be summarized by tabulating the number (and percentage) of events occurring in each treatment arm. All participants who receive at least one dose of treatment will be included in the safety analysis. Mis-randomised participants will be analysed as treated. Adverse drug reactions (ADRs) will be summarized by severity using the preferred term and the worst severity and causality recorded. The worst case will be assumed if severity or causality are missing. All participants who experience treatment-emergent ADRs will be listed including participant identification, treatment arm, system organ class, preferred term, unexpectedness, seriousness, severity, start and stop dates/times, action taken and outcome.

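### No baseline adjustment is specified for the total adenoma count (end-point iii), although the baseline count is recorded; adding it costs nothing and may give a modestly more precise rate ratio

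*Protocol article*

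**What the plan says.** All of this is in the Statistical analysis part of the protocol article.

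- **Total count (end-point iii), Secondary analyses:** "Number of adenomas per participant at the first BCSP surveillance colonoscopy will be analysed using a Poisson regression model". The sentence ends there, with no covariate and no robust errors.
- **Advanced count (end-point ii), Secondary analyses:** this "will be analysed using a Poisson regression model with robust standard errors". Again no covariate is named.
- **Location of adenomas (end-point iv), Secondary analyses:** this "will be explored, possibly using a Poisson random effects model with bivariate response", in which "treatment and a baseline polyp count will be independent variables together with random intercepts corresponding to patient and BCSP Centre".
- **Descriptive analyses:** the baseline variables include the "number of adenomas detected at baseline" and the corresponding advanced count.
- **Primary analyses:** a secondary adjusted analysis of the binary primary end-point uses the repeat-endoscopy indicator "plus any other covariates identified as important from the baseline comparisons". This provision covers the primary outcome only.

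**The concern.** The total surveillance count and its left/right split are the same adenomas counted in two ways. The section names the baseline count for the split and not for the total.

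Participants enter with at least three adenomas and no upper limit (Participants section), so entry counts will vary. Randomisation is stratified by centre only (Intervention section), so the design does not balance that variation. If people who enter with many adenomas tend to form more again, an unadjusted model leaves predictable between-person variation in the error term and the confidence interval is wider than it need be.

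This matters for end-point iii because it is the outcome closest to the 22.4% net fall in adenoma number in the familial adenomatous polyposis trial that motivates the study. Precision is also expensive here: the Discussion reports 15–20% eligibility against a predicted 60%.

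**Working it through.** **The plan's own figures.** The article gives no mean, dispersion, precision or power for either count end-point. Its sample size, "with 80% power at a 5% two-sided significance level", is for the binary primary end-point. The 678 reproduces as 2 × 339 for 60% against 49% with a continuity correction, and 768/0.85 = 904. These figures fix the evaluable number (192 × 4 = 768) but do not test the present point.

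**Assumed inputs**
- Baseline count: 3 plus a negative binomial with mean 3 and shape 1.5. Mean 6; variance 3 + 9/1.5 = 9.
- Untreated mean of about 1.5 adenomas at surveillance. With dispersion 1 this matches the plan's 60% recurrence: 1 − 1/(1 + 1.5) = 0.60.
- Dispersion φ of 0.5 or 1.0 (variance = mean + φ × mean²).
- Slope of log expected count on log baseline count: 0 to 1.0.
- Each drug has rate ratio 0.78 or 0.82.

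**Simulated variance of the EPA log rate ratio, adjusted ÷ unadjusted** (robust errors in both models, 400 trials per setting)

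| Slope | Rate ratio | φ = 0.5 | φ = 1.0 |
|---|---|---|---|
| 0 | 0.82 | 1.000 | 1.001 |
| 0.3 | 0.82 | 0.988 | 0.990 |
| 0.5 | 0.78 | 0.963 | 0.972 |
| 0.6 | 0.82 | 0.951 | 0.958 |
| 0.8 | 0.78 | 0.905 | 0.931 |
| 1.0 | 0.82 | 0.859 | 0.887 |
| 1.0 | 0.78 | 0.855 | 0.891 |

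The rows with rate ratio 0.82 set recurrence on double placebo to 60%; those with 0.78 set the untreated mean to about 1.5. In the 0.82 runs the estimated rate ratio was about 0.81–0.82 with or without the covariate, so adjustment does not change the quantity estimated.

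**Check by formula at slope 1.0.** Let m be the mean count and c² the squared coefficient of variation of the rate predicted from baseline. Per participant, the variance of the log mean is approximately:
- unadjusted: 1/m + (1 + φ)(1 + c²) − 1
- adjusted: 1/m + φ(1 + c²)

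The difference is c², which at slope 1.0 is 9/36 = 0.25. Averaged over the four arms at rate ratio 0.78, m = 1.5 × 0.89 × 0.89 = 1.19, so 1/m = 0.84.
- φ = 0.5: 0.25/(0.84 + 0.875) = 14.6%
- φ = 1.0: 0.25/(0.84 + 1.5) = 10.7%

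These agree with the simulated 14.5% and 10.9%.

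**In familiar units (total count).** The largest fall in standard error is 1 − √0.855 = 7.5%. In equivalent evaluable participants, a ratio of 0.972 is 768 × (1/0.972 − 1) = 22, and 0.855 is 768 × (1/0.855 − 1) = 130. Those two figures belong to slopes 0.5 to 1.0. At slope 0.3 (ratio 0.99) the gain is about 8, and at slope 0 it is nil. In the 0.82 runs power moved by under 3 points up to slope 0.6, and by about 2 to 7 points at slope 1.0.

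**Advanced count.** The Background reports that 86% of recurrent adenomas at one year were small and non-advanced, so the untreated mean is about 0.14 × 1.5 = 0.21. Averaged over arms this is 0.21 × 0.89 × 0.89 = 0.166, so 1/m = 6.0. The 1/m term now dominates: at slope 1.0 the fall is 0.25/(6.0 + 0.875) = 3.6% or 0.25/(6.0 + 1.5) = 3.3%. Simulation with log baseline total count as covariate gives about 0.3% at slope 0.3, 1% at slope 0.5 and about 4% at slope 1.0.

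**Robust errors for end-point iii.** If the total-count sentence is taken literally, model-based Poisson errors assume variance equal to the mean. Under the assumed dispersion, variance ÷ mean is 1 + 1.19 × 0.5 = 1.59 to 1 + 1.19 × 1.0 = 2.19. The true standard error would then be √1.59 = 1.26 to √2.19 = 1.48 times the model-based one.

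**The case against.** The strongest objection is that silence is not exclusion. The two count sentences list no model terms at all, not even the treatments. The article condenses a fuller protocol, and covariate lists for secondary models are often left to that or to the analysis plan. A reader might infer that the plan rules out baseline adjustment; the text does not say so. What remains is that this section does name covariates where it wants them, for the adjusted primary analysis and for the location model. As written, the count analyses specify none.

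A reader might also infer that the count analyses are biased or invalid. They are not: an unadjusted randomised comparison remains valid.

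A third tempting reading is that the plan contradicts itself on both count end-points. It does not. The location model is only a possibility, is built for a different question and does not mention advanced adenomas. It is a comparator for end-point iii alone, and a weak one.

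Finally, the precision loss is conditional. The article gives no baseline-outcome association. It recruits high-risk patients because recurrence is higher (over 60% at 12–15 months, against 25–50% at three years in trials of roughly intermediate-risk patients). That comparison across cohorts suggests a direction but gives no slope within this trial. With a weak association the gain is close to nothing.

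**Conclusion.** The point holds as a modest, conditional improvement to end-point iii. No baseline adjustment is specified for the total adenoma count, and the result may be less precise than the data allow. The variance reduction is about 0% to 15% over assumed slopes of 0 to 1.0, and reaches double figures only towards the top of that range. For end-point ii it is about 0% to 4%, so the equivalent of 22 to 130 participants must not be carried over to advanced adenomas.

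All these figures rest on the assumed baseline distribution, mean count, dispersion and slope. The advanced figure also rests on the 86% non-advanced share in the audit cohort and on using the baseline total as covariate. The documents support neither a definite loss nor any bias in the rate ratio. The missing mention of robust errors for end-point iii should be put right in the same edit, because it affects the width of the interval if the sentence is followed literally.

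**What to change.** In the Secondary analyses section, or in the analysis plan that implements it:

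1. **End-point iii:** fit the Poisson model with both treatments, log baseline total adenoma count and robust standard errors, as the advanced-count sentence already has. Report the adjusted rate ratio as the result and show the unadjusted one beside it.
2. **End-point ii (optional):** add log(baseline advanced count + 1), with robust errors as planned. Little gain is expected.

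State this before unblinding, so that the choice between adjusted and unadjusted results is not made afterwards.

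The cost is one covariate per model and a sentence of text. The counts are already recorded, and nothing changes in conduct or sample size. If the baseline count proves not to be prognostic, essentially nothing is lost: the variance ratio at slope 0 is 1.00.

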## Discussion

The first patient first visit (FPFV) of the Trial was 11th November 2011. It soon became clear from screening logs at individual BCSP sites that the eligibility rate was 15–20% rather than the 60% that had been predicted in the original sample size calculation. One contributing factor was the use of other non-aspirin anti-platelet agents such as clopidogrel, which we later added as an extra exclusion criterion (Protocol version 3.1 dated 12 Jan 2012), in order to completely rule out the possibility of excess bleeding risk due to concomitant use of three agents with anti-platelet activity in one arm of the Trial. Another major contributing factor was the larger than expected number of ‘high risk’ individuals (approximately 25%) who required a repeat endoscopy, which was an exclusion criterion in earlier versions of the Trial protocol. We obtained data on the proportion of ‘high risk’ patients undergoing a repeat endoscopic procedure from participating BCSP sites and demonstrated that there had been a consistent increase in the number of patients undergoing repeat ‘re-look’ procedures since the start of the BCSP in 2006 and that ‘re-look’ rates varied significantly across BCSP sites. ‘High risk’ patients, who require a repeat screening procedure, were originally excluded from the Trial on the basis that the primary end-point might be confounded by adenoma detection and removal at an extra endoscopic procedure in-between the screening and one-year surveillance procedures. However, subsequent analysis (in April 2012) of the North-East BCSP Hub (9 BCSP Centres) and the Southern BCSP Hub (17 BCSP Centres) data on ‘high risk’ patients who underwent one-year surveillance colonoscopy in 2010 did not support this notion. Of 1,189 ‘high risk’ patients, 930 (78%) went straight to one-year surveillance after a single screening colonoscopy. One or more adenomas were detected in 465 (63%) of 738 patients, for whom data were available. The corresponding adenoma detection rate for ‘high risk’ patients, who underwent a repeat partial colonoscopy or flexible sigmoidoscopy within 3 months of the initial screening colonoscopy was 54% (59/110), but the adenoma detection rate in patients who underwent a repeat full colonoscopy was 67% (56/83). The overall adenoma detection rate at first surveillance colonoscopy was 62%, which is consistent with the value (60%) used in our original sample size calculation, although the cohort included patients who had undergone a repeat screening endoscopy. Therefore, we amended the protocol in order to allow recruitment of those individuals who require no more than one repeat endoscopic procedure (either colonoscopy or flexible sigmoidoscopy) within the 3-month screening episode window (Protocol version 4.0 dated 24 May 2012).

At the time of the latest sample size estimate in April 2012, we assumed that drop-out would be 10% rather than 15% (based on existing BCSP Trial site experience) and noted that 27 participants had already been recruited meaning that a further (768/0.9 = 853) – 27 = 826 participants were required. Data from the first 5 months’ recruitment experience and from the above 2010 BCSP Hub data indicated that approximately 24% of ‘high risk’ patients underwent a repeat endoscopy within 3 months of the first screening colonoscopy and that 27% of ‘high risk’ patients who were excluded because of the need for a repeat colorectal endoscopic procedure also met an additional exclusion criterion. Therefore, we estimated that the percentage recruitment could be increased from 15% (the current percent recruitment rate) to 15% + 17.5% (24% × 0.73) = 32.5%. Rounding the recruitment rate down to 30%, we estimated that the remaining number of ‘high risk’ individuals that would need to be screened from April 2012 to obtain 768 evaluable ‘high risk’ individuals is 827/0.3 = 2,757.

Revised Trial timelines are currently based on an overall ‘high risk’ patient recruitment rate of 30% and identification of approximately 50 ‘high risk’ patients by a BCSP Centre per year (this estimate has been confirmed by our data on the number of ‘high risk’ patients screened for the Trial by open, participating Centres, so far). In order to compensate, for the reduced percentage recruitment estimate, the number of participating BCSP Centres has been increased from 15 to 30 (equivalent to approximately 60 separate BSCP endoscopy sites throughout England).

The ability to recruit patients who have been identified as ‘high risk’ via FS screening, as well as by faecal occult blood test screening, should also increase the recruitment rate of the Trial, as the Bowel Scope programme is rolled out across England over the next two years.

The seAFOod Polyp Prevention Trial is the first Clinical Trial of an Investigational Medicinal Product (CTIMP) in the BCSP. The experience gained from the set-up and intervention phases of the Trial will be invaluable for the design of subsequent intervention trials in the BCSP. Early experience has confirmed that the BCSP is an excellent framework for a CRC chemoprevention RCT.

